## Abstract

**Background:**

Only one-third of hypertensive patients achieve and maintain blood-pressure control. This is attributed to low treatment adherence and has a negative impact on clinical outcomes. Adherence is multidimensional and involves aspects both related to patient characteristics and to the chronic nature of the disease. In this context, motivational interviewing has been proposed as an approach to foster patients’ motivations to change their behavior for the benefit of their own health, thus providing more lasting behavioral changes.

**Design and methods:**

Single-center, parallel, randomized controlled trial with outcome-assessor blinding. This study will select adult patients (*n* = 120) diagnosed with hypertension who receive regular follow-up in a specialized outpatient clinic. Patients will be randomly allocated across two groups: the intervention group will have appointments focused on motivational interviewing, while the control group will have traditional appointments. Patients will be monitored face-to-face, once monthly for six months. The primary outcomes will be a reduction of at least 8 mmHg in systolic blood pressure and changes in mean blood pressure measured by 24-h ambulatory blood pressure monitoring. Secondary outcomes include improvement of adherence to a low-sodium diet, adherence to self-care behaviors, regular use of antihypertensive medications, increase or maintenance of physical activity, weight reduction, evaluation of changes in daytime sleepiness, and cessation of smoking.

**Discussion:**

This study shows an intervention strategy that will be tested and, if effective, warrant replication in monitoring of other chronic diseases.

**Trial registration:**

ClinicalTrials.gov, NCT02892929. Registered on 24 August 2016.

**Electronic supplementary material:**

The online version of this article (10.1186/s13063-019-3486-1) contains supplementary material, which is available to authorized users.

## Background

Hypertension is a highly prevalent cardiovascular risk factor, as well as the most common condition seen in primary care. Uncontrolled hypertension is the main risk factor for cardiovascular disease, which, in turn, is the leading cause of death in the world [1, 2]. Studies have demonstrated that increased risk starts at blood pressure (BP) values as low as 115/75 mmHg, doubling with each 20 mmHg rise in systolic blood pressure (SBP) or 10 mmHg rise in diastolic blood pressure (DBP) [3].

Poor BP control is associated with low treatment adherence [4–6]. However, because it is a multidimensional phenomenon, adherence is not determined only by issues inherent to patients themselves; disease-related factors, health beliefs, lifestyle, and cultural habits also play important roles [6, 7]. Approximately two-thirds of patients treated for hypertension fail to achieve and maintain adequate BP control [8, 9]. Studies suggest that adherence to self-care behaviors and lifestyle modifications can reduce BP levels [4, 8].

Several interventions to promote lifestyle modifications and self-care behaviors have been proposed. Motivational interviewing (MI), developed by Miller and Rollnick, is a person-centered, directive counseling method designed to stimulate and strengthen personal motivation for change by exploring and resolving ambivalence [10–12]. It is a guiding style meant to enhance intrinsic motivation to change, develop autonomy, and promote behaviors in the interest of health [11, 13]. The practice of MI is based on the following guiding principles: listen with empathy; avoid argumentation and confrontation; roll with resistance; and sustain effectiveness and optimism [13].

In 2008, Ogedebbe et al. tested, in a randomized controlled trial (RCT), the effect of MI counseling versus usual care on medication adherence and BP in 190 African Americans with hypertension. The intervention group received standard care plus four sessions of MI at three-month intervals for a period of one year. The primary outcome was adherence to prescribed antihypertensive medication; the secondary outcomes were changes in office BP, self-efficacy, and intrinsic motivation at baseline and 12 months. The authors found no significant reductions in SBP between groups and no improvement in medication adherence in the intervention group [14]. More recently, in 2012, Ogedegbe et al. tested positive affection induction and self-affirmation strategies as a potential means of improving adherence to drug therapy by African American patients with hypertension. Their results suggested that this intervention was more effective in improving adherence to antihypertensive drug therapy compared with patient education alone [15]. In 2016, Boutin-Foster et al. assessed the effect on BP control of a combination of positive affection and self-affirmation strategies (including MI) compared with conventional educational measures in hypertensive African American patients over a one-year period, with bi-monthly telephone follow-up. This study had several limitations, e.g. at baseline patients in the intervention and control groups both received an educational workbook with the etiology of hypertension, treatment options, and lifestyle changes that one could make to improve BP control and to support goalsetting, and the same research assistants led appointments in the intervention and control groups. The results were not positive for a reduction in BP [16].

In the context of other chronic co-morbidities, Creber et al. compared MI versus usual care in patients with heart failure. The intervention consisted of one home-based motivational interview and three or four follow-up calls. The authors reported improvement of self-care in the MI group [17].

The few existing studies carried out using this intervention showed limited effects on BP lowering with the MI approach. However, some results obtained to date were difficult to generalize because they were tested in a specific population (hypertensive African Americans); other studies used a combination of MI and other strategies; in others, interventions were not face-to-face. Furthermore, none used 24-h ambulatory blood pressure monitoring (ABPM) to measure BP; ABPM findings are now known to be associated more strongly with cardiovascular outcomes than office measurements [18, 19]. We designed this RCT to compare the effectiveness of MI versus usual care in reducing SBP and DBP, measured by ABPM, in patients with hypertension. The intervention will consist of an exclusive MI approach applied monthly in face-to-face appointments over a six-month follow-up period.

## Methods/Design

### Study design

The “effect of MotIvational iNterviewing In HyperTensive patients” (MIdNIgHT) study is a randomized, single-center, parallel clinical trial with a follow-up period of six months. Patients with hypertension will be enrolled from Hospital de Clínicas de Porto Alegre (HCPA), a center in southern Brazil, and invited by telephone to participate in the trial. After a baseline evaluation, participants will be randomly allocated into two groups: (1) an MI intervention group (IG); and (2) a control group (CG) to receive usual care. MI sessions and standard clinical assessments (usual care) will be conducted face-to-face once monthly for six months. Anthropometric measurements, questionnaires and scales (Self-Care of Hypertension Inventory [SC-HI], Medication Assessment Questionnaire [MAQ], Dietary Sodium Restriction Questionnaire [DSRQ], International Physical Activity Questionnaire [IPAQ], Epworth Sleepiness Scale [ESS]), and ABPM will be performed at baseline and at the end of follow-up.

A flow diagram of the study design is presented in Fig. 1. The study timeline and schedule of enrollment, interventions, and assessments (Standard Protocol Items: Recommendations for Interventional Trials [SPIRIT] figure) and the SPIRIT Checklist are provided as Fig. 2 and Additional file 1, respectively.

**Fig. 1 Fig1:**
[figure not shown]
*Flow diagram* of the study

**Fig. 2 Fig2:**
[figure not shown]
Schedule of enrollment, interventions, and assessments

### Inclusion and exclusion criteria

The study will include female and male adults (aged 18–80 years) who have been receiving treatment and follow-up at the HCPA outpatient hypertension clinic for > 6 months. Patients must be on at least two antihypertensive medicaments at the time of recruitment and must not have been seen by a nutritionist or followed nutritional guidance in the last six months.

The exclusion criteria will be: pregnancy or lactation; gastrointestinal tract disease; inflammatory disease; chemotherapy; diagnosed diabetes; incapacity to engage in an interview due to intellectual disability or dementia, defined by application of a cognitive deficit assessment questionnaire [20]; and/or incapacity to participate in the intervention program without the need for third-party involvement.

### Ethical considerations

All patients will read and sign an informed consent form before inclusion (Additional file 2). The study protocol was approved by the HCPA Research Ethics Committee with opinion number 160225, registered in the ClinicalTrials.gov database with accession number NCT02892929, and will be conducted in accordance with the principles of the Declaration of Helsinki and the Ethical Principles for Medical Research Involving Human Subjects of the National Health Council of Brazil [21].

### Outpatient hypertension clinic and staff approach

The HCPA outpatient hypertension clinic is a multidisciplinary clinic attended by approximately 150 hypertensive patients per month. The clinic provides regular monitoring to optimize and encourage adherence to drug therapy and management of hypertension-related co-morbidities. Appointments are led by specialized cardiologists, pharmacists, psychologists, researchers, and graduate students.

### Lead researcher training

The lead researcher is a specialist cardiovascular nurse with 10 years of experience in the care of patients with heart disease and will be responsible for application of the MI technique during appointments in the intervention group. She has participated in an intensive MI workshop which followed the recommendations of the Motivational Interviewing Network of Trainers [22] in 2013 and, more recently, in 2015, 2016, and 2018, participated in workshops on advanced MI techniques. During the study, monthly supervision will be provided by another MI specialist. Schwalbe et al. [23] showed that 3–4 post-workshop supervision sessions over a period of six months were enough to maintain the effects of training on MI skills. Training and the supervision will be the responsibility of a PhD researcher in Psychiatry with longstanding expertise in MI and personal training conducted in the United States with Miller and Rollnick.

### Sample size

The sample size was calculated with WinPepi 11.20 software. Delta values of BP levels for the study population as reported by Correa et al. (4.4 mmHg for 24-h SBP and 2.7 mmHg for 24-h DBP) were used [24]. The sample size was estimated at 100 patients, 50 in the IG, and 50 in the CG, considering a difference in SBP of 8 mmHg between groups, a standard deviation of 14 mmHg, 80% power, and alpha = 0.05. To account for 20% attrition, the sample will consist of 120 patients, 60 in each group.

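### The attrition allowance is computed the wrong way round: 120 patients with 20% loss leave 96, not the required 100, though power falls by less than one point

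*Protocol article*

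**What the plan says.** The Sample size section of the protocol article gives the inputs and two sizes.

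- Requirement before losses: "The sample size was estimated at 100 patients, 50 in the IG, and 50 in the CG".
- Inputs: "considering a difference in SBP of 8 mmHg between groups", "a standard deviation of 14 mmHg" and "80% power, and alpha = 0.05".
- Enrolled size: "To account for 20% attrition, the sample will consist of 120 patients, 60 in each group".

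No other section describes an allowance for losses. The Study protocol section commits to analysis by intention to treat and provides reminder calls and rescheduling of missed appointments. It does not say how a missing six-month recording enters the analysis. Under Outcomes of interest, the blood pressure outcomes come from ambulatory monitoring at the first and last visits only.

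**The concern.** The section fixes three figures: 100 needed, 20% lost, 120 enrolled. Any two of them determine the third, and the three given disagree. Attrition is a fraction of those enrolled, so the number left is 120 × (1 − 0.20), and that is not 100.

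What is at stake is a stated figure against which readers will check the trial. If attrition turns out exactly as planned, the trial will end with fewer evaluable patients than its own requirement, although the protocol says the allowance covers that loss. A patient without a six-month ambulatory recording has no observed blood pressure endpoint, so losses reduce the information on the primary outcome directly.

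**Working it through.** **Inputs, all from the Sample size section.** Difference δ = 8 mmHg, SD σ = 14 mmHg, power 80%, α = 0.05, equal arms, 20% attrition, 120 enrolled. The section does not say whether the test is one- or two-sided. I take it as two-sided because that reproduces the stated size; a one-sided test gives 38 per arm and does not.

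**Step 1: reproduce the requirement of 100.**

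Normal approximation: n per arm = 2(z₀.₉₇₅ + z₀.₈₀)²σ²/δ² = 2 × (1.960 + 0.842)² × 196/64 ≈ 48.1, rounded up to 49 (98 in total).

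Noncentral t: 49 per arm gives 79.96% and 50 per arm gives 80.8%, so 50 is the smallest arm that reaches 80% (100 in total). The stated 100 is correct.

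**Step 2: reproduce the 120.**

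- Adding 20% to the requirement: 100 × 1.20 = 120. This is the protocol's figure.
- Dividing by the retained fraction: 100/(1 − 0.20) = 125. With equal arms, 50/0.80 = 62.5, so 63 per arm and 126 in total.

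**Step 3: what 120 delivers.**

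- Left after 20% loss: 120 × 0.80 = 96, or 48 per arm, which is 4 below 100.
- Largest loss that leaves 100: 1 − 100/120 = 16.7%.

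**Step 4: is this only rounding in the 100?** Take the smaller normal-approximation requirement of 98. Then 98/0.80 = 122.5, so 123 in total, or 124 with equal arms (62 each). The tolerable loss becomes 1 − 98/120 = 18.3%. On this basis too, 120 does not cover 20%.

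**Step 5: power.** The noncentrality is δ/(σ√(2/n)). At n = 48 it is 8/(14 × √(2/48)) = 2.80. The normal approximation then gives Φ(2.799 − 1.960) = Φ(0.839) = 79.9%; the noncentral t on 2 × 48 − 2 = 94 degrees of freedom gives 79.1%.

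| Evaluable per arm | Power, normal | Power, noncentral t |
|---|---|---|
| 48 (120 enrolled, 20% lost) | 79.9% | 79.1% |
| 49 | 80.7% | 79.96% |
| 50 (stated requirement) | 81.5% | 80.8% |
| 60 (no loss) | 87.9% | 87.4% |

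Against the stated 80%, the gap at 48 per arm is 0.1 points (normal) or 0.9 points (noncentral t). Expressed as an effect, the smallest difference with 80% power at 48 per arm is 8.09 mmHg by the noncentral t, against the planned 8.

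**The case against.** The strongest reply is that nothing of practical weight follows. Adding the attrition percentage to the requirement is a common shortcut. Power at the planned loss is 79–80%, which no one would call different from 80%. The protocol takes steps to limit losses, and nothing in it shows that attrition will reach 20%. The 16.7% also depends on the rounded requirement of 100; starting from 98, the tolerable loss is 18.3%.

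All of this bears on the size of the point, and it stands as far as it goes: the matter is minor. It does not make the sentence true. The shortcut does not leave 100 patients, and under either requirement 120 falls short of covering 20%. Nor is this a detail left to a fuller document, since the section itself fixes all three numbers.

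Two stronger readings are tempting, and the document supports neither.

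- A reader might infer that the trial is underpowered. The protocol's own inputs put the shortfall below one percentage point at the attrition it plans for. Comparing 79.1% with the 80.8% at 50 per arm overstates the gap, because the protocol claims 80%, and the 0.8 above that is a surplus from rounding up.
- A reader might infer that a baseline-adjusted analysis will make up the shortfall. The Statistical analysis section lists the t-test or Mann–Whitney test, generalized estimating equations, repeated-measures analysis of variance, and analysis of covariance, and names none as primary. The protocol gives no correlation between baseline and six-month values, and it does not say whether the SD of 14 mmHg refers to a single measurement or to a change. A gain from adjustment cannot be calculated from the text.

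**Conclusion.** The point holds as a minor error, wrong as written. The requirement of 100 reproduces, but its inflation to 120 does not cover the 20% attrition claimed for it. At 20% loss 96 patients remain, 4 short; 120 covers 16.7% loss; and covering 20% takes 125, or 126 with equal arms.

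The head counts rest only on the protocol's own three figures. The power figures of 79.1% to 79.9% rest on a two-sided 5% test, an unadjusted comparison of two means, 8 mmHg and SD 14 as stated, and equal loss in the arms. The primary outcome is also worded as a reduction of at least 8 mmHg, which could be read as a responder endpoint; the power figures do not apply to that reading.

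**What to change.** Keep 120 and restate the final sentence of the Sample size section, for example: *120 patients (60 per group) allow for about 16.7% attrition; at 20% attrition 96 remain evaluable, with about 79–80% power in an unadjusted two-sided comparison.* The cost is one sentence and a slightly less favourable stated figure. The design, recruitment target and analysis stay as they are.

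If the sponsor prefers to keep the 20% claim literally, the enrolled number must become 126 (63 per group), 6 more patients. Recruitment was still open, with 50 included, when the article was written (Trial status), so that was possible then. A gap of under one point of power does not call for it.

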### Study protocol

Patients will be identified by the HCPA hypertension clinic appointment schedule and invited to participate in the study. The first appointment will serve to obtain informed consent and confirm eligibility. Then, the patient will be randomized to either IG or CG. Participants of both groups will attend a total of six monthly appointments, scheduled by prearrangement, at the HCPA Clinical Research Center. At the first and last protocol visits, the clinical and sociodemographic questionnaire and the other study instruments will be applied, anthropometric measurements will be obtained, and the 24-h ABPM device will be placed. Each appointment will have an average duration of 30 min. Patients will be reminded of consultations the day before via phone calls; missed appointments will be rescheduled. Appointments should take place within a one-week interval of the 30-day time point since the preceding visit. The primary outcome of the study will be a reduction of at least 8 mmHg in SBP and changes in DBP and mean BP, all assessed by 24-h ABPM. The secondary outcomes will include improvement of adherence to a low-sodium diet, adherence to self-care behaviors, regular use of antihypertensive medications, improvement or maintenance of levels of physical activity, changes in daytime sleepiness, weight loss, and cessation of smoking. These outcomes will be assessed by appropriate questionnaires (described in detail below); weight loss will be measured directly during visits and cessation of smoking will be self-reported. Analysis will follow the intention-to-treat principle. All collected data will be stored in Microsoft Excel spreadsheets and tabulated by the double data entry method. The results of the trial will be communicated to the participants in a meeting organized at the end of the study.

### Randomization, allocation, and confidentiality

The first study visit will consist of confirmation of eligibility, completion of the informed consent form, and collection of sociodemographic and clinical data. After this initial visit, patients will be allocated to the CG or IG by simple random sampling, using opaque numbered envelopes, each containing a randomization code. The list of computer-generated randomization codes, generated online in blocks of six at <http://www.randomization.com>, will remain in the possession of an independent investigator not otherwise involved in the study.

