### Study variables, blinding, and methods of assessment

The research team will be responsible for the screening and selection of eligible participants. Three team members will obtain written informed consent before study enrollment. Researchers will not be blinded to participant intervention. However, the researcher responsible for application of the MI technique and the one responsible for conducting conventional appointments will be blinded to the outcomes of the study. The participants will be blinded to group allocation and primary outcome. The investigators who are not outcome-blinded will be trained to obtained standardized anthropometric and BP measurements as well as to administer the study questionnaires.

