### Potential biases

This study has some limitations. The questionnaires and scales used to measure secondary outcomes are self-reported and thus subject to a range of biases, such as regarding credibility. The open-label design also introduces some potential for bias and the sample size limits the external validity.

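### Allocation is labelled simple random sampling but uses fixed blocks of six, so unblinded recruiters who track past allocations could know up to a quarter of assignments in advance

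*Protocol article*

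**What the plan says.** Under Randomization, allocation, and confidentiality, the protocol article states that after the initial visit "patients will be allocated to the CG or IG by simple random sampling, using opaque numbered envelopes, each containing a randomization code". The next sentence says that the list of codes was "generated online in blocks of six at" a named website and "will remain in the possession of an independent investigator not otherwise involved in the study". Six is the only block size given, and no stratification is mentioned.

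Other sections describe the setting:

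- Study design: the study "is a randomized, single-center, parallel clinical trial with a follow-up period of six months".
- Sample size: "the sample will consist of 120 patients, 60 in each group".
- Study variables, blinding, and methods of assessment: "The research team will be responsible for the screening and selection of eligible participants", and "Researchers will not be blinded to participant intervention".
- Potential biases: "The open-label design also introduces some potential for bias".
- Intervention group and Control group: a nurse delivers the motivational interviewing (MI) visits and a nutritionist delivers the control visits, so a patient's arm is visible from whom they see.
- Trial status: recruitment was under way, with 50 patients included.

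**The concern.** There are two problems, of different weight.

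1. **The label.** Simple randomisation draws each allocation independently and forces no balance. Blocks of six force three patients per arm in every block. One procedure cannot be both.

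2. **The fixed block size.** Once one arm has received three patients within a block, the rest of that block is determined. Opaque envelopes and independent custody hide the list, but they do not stop someone from working out the next code from allocations already known. Here the people who select patients can know earlier allocations, there appears to be a single sequence, and the block size is in print.

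What is at stake is selection bias at enrolment. A recruiter who expects a given arm next could, even without intending to, invite or defer a patient according to how ready for change that patient seems. That trait bears directly on response to MI. Blinded outcome assessment, ambulatory monitoring and intention-to-treat analysis all act after enrolment and cannot undo it. Baseline adjustment may not help either, because none of the listed baseline questionnaires is named as a measure of motivation.

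**Working it through.** **Which method is in use.** The planned 120 patients make 120 / 6 = 20 complete blocks, each 3:3, which reproduces the stated 60 per arm exactly. Under true simple randomisation an exact 60:60 split has probability C(120,60) / 2^120 = 0.073. The stated split fits the blocks, not the label.

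**Certain allocations in a 1:1 block of six.** There are C(6,3) = 20 equally likely sequences. An allocation is certain once one arm has been used up.

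| Position | Condition | Probability certain |
|---|---|---|
| 1 to 3 | cannot occur | 0 |
| 4 | first three in the same arm: 2/20 | 0.10 |
| 5 | last two in the same arm: 2 × 4 / 20 | 0.40 |
| 6 | always | 1.00 |

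The sum is 1.5 per block, or 1.5 / 6 = 25%. The closed form 2m/(m+1) with m = 3 gives the same 1.5. Over 20 blocks this is 20 × 1.5 = 30 of 120.

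**Still to come.** Assume that the 50 included were all allocated in sequence. Then 50 = 8 × 6 + 2, so the next patient takes position 3 of the ninth block. That block still has all its positions that can be certain, and 11 full blocks follow: 12 × 1.5 = 18 of the remaining 70.

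**Best guess.** Always name the arm that is behind, and toss a coin when the arms are level. Expected correct guesses per block are m + (2^(2m)/C(2m,m) − 1)/2 = 3 + (64/20 − 1)/2 = 4.1, and 4.1 / 6 = 68.3%, against 50% under simple randomisation. This strategy needs only the running totals. Certain knowledge also needs the block size.

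**After the change.** In simulation with sizes 4, 6 and 8 in random order, where the recruiter knows the set of sizes but not their order, about 2.3% of allocations are certain. With sizes 4 and 6 the figure is about 5.5%. For the 66 patients left after the open block is completed, the expected number falls from 11 × 1.5 = 16.5 to about 0.023 × 66 = 1.5. The best-guess rate hardly moves: the same formula gives 2.83 of 4, 4.1 of 6 and 5.33 of 8, and (2.83 + 4.1 + 5.33) / 18 = 68.1%.

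**Final imbalance after the change.** An unfinished last block of eight can leave at most 4. If the old list stops inside a block, that block can add up to 3, giving 7. At position 2, where 50 allocated patients would leave it, it can add 2, giving 6.

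**The case against.** The strongest reply is that 25% describes an ideal observer. It needs someone who recruits, knows the block size, and holds every earlier allocation in envelope order. The article says that researchers are not blinded; it does not say that those who take consent keep the sequence. Allocation follows eligibility, consent and baseline data collection. If several patients are between invitation and allocation at once, the next envelope cannot be tied to a particular patient when that patient is selected. The article does not say how often this happens. Nor does it say who opens the envelopes, and the single unstratified sequence is inferred from its silence on stratification. Most entry criteria are objective, which narrows discretion.

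Much of this stands. The 25% must be read as a ceiling that depends on full tracking, and the label alone is a one-phrase correction, since the next sentence identifies the method.

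What does not stand is the idea that envelopes and independent custody settle the matter, because deduction from past allocations needs no access to the list. Objective entry criteria also leave open whom to invite and when, and one exclusion, inability to take part without a third party's help, calls for judgement.

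A reader might go further and infer that a quarter of allocations were in fact known, or that patients were selected on motivation. The documents support neither: they show opportunity and report no instance of prediction.

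**Conclusion.** The point holds as a wording error together with an avoidable weakness in the design. The method described is permuted-block randomisation with one fixed block size. For a recruiter with complete tracking, on average up to 25% of allocations (30 of 120) would be certain and up to 68% could be guessed correctly. About 18 certain allocations would fall among the 70 patients still to come.

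These figures assume 1:1 blocks, a single unstratified sequence, knowledge of the block size (for the certain allocations only), and knowledge of all earlier allocations in order. The figure of 18 also assumes that the 50 included patients were all allocated in sequence. Less knowledge gives smaller numbers. The arithmetic is exact. How far bias would follow is uncertain and cannot be sized from the document. The change should be made, but the weakness does not invalidate the randomisation.

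**What to change.** 1. Replace the simple random sampling label with *permuted-block randomisation*.
2. Complete the currently open block of six from the existing list.
3. For all later patients, have the independent investigator issue new sealed, opaque, numbered envelopes from a list with randomly varied block sizes (for example 4, 6 and 8). Keep the sizes from the recruiting team and out of print until enrolment closes. Record the envelope number at which the switch is made.

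The cost is one new list, one set of envelopes and a possible final imbalance of at most 4 patients, or up to about 7 if the open block is not completed first. No clinical procedure changes.

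The gain is the near removal of certain knowledge. The 68% guessing rate stays for anyone who tracks the running totals, so those who invite patients should also, where practicable, not see the record of earlier allocations. If enrolment has already finished, only the wording correction and a stated limitation remain.
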